#### Risk Management Protocol

Risk management procedures were developed collaboratively with the participating universities, on-campus counselors, online program providers (ie, GAD Online and Lantern), and the research team. All students will be provided with the contact information for the respective on-campus counselor at the start and finish of the online survey. In this way, anyone exposed to the survey will be informed about currently accessible services. Furthermore, all universities have agreed to increase the current time of the existing on-campus counselor should student demand require it. In addition, for any individual in the guided intervention (Lantern), program coaches will monitor for worsening symptoms and express student preference to receive more intensive treatment and provide a referral to the on-campus counselor as necessary. Additionally, if a student in the guided program indicates thoughts of harm to self or others, the coach will notify the coach clinical supervisor (a clinical instructor at Stanford and licensed mental health care professional in the United States) via email and the campus-specific, on-site counselor via phone. Both will help determine how best to manage the situation, and the on-campus counselor will intervene and reach out to the student as necessary. In the consent, students are informed that confidentiality can be breached should the student indicate harm to self or others. Those in the unguided intervention will be explicitly informed that their actions in the program are not monitored and that they should contact the on-campus counselor should they want live support. They will again be reminded of the contact information of the on-campus counselor when they are assigned into this unguided intervention.

#### Sample Size Estimation

The sample size estimation is based on detecting differences in GAD symptom severity change (measured using dimensional scoring of the GAD-Q-IV) from baseline to post- and follow-up assessments between each active conditions and the wait-list control group. Treatment trials of online, CBT-based, guided self-help interventions for GAD have found an average large effect size of roughly 1.07 relative to a wait-list control group using the GAD-Q-IV [38]. In this study, more than half of the treated participants had recovered according to a structured interview, suggesting that a treatment effect size of 1.07 is clinically meaningful. Treatment trials of purely self-help interventions for subthreshold and clinical anxiety have found smaller yet still promising effect sizes ranging from 0.62 to 0.84, respectively, relative to a wait-list control group [31].

To enable detection of difference in mean change between each active intervention and the control group, the sample size is powered to detect at least a medium effect size of 0.5. With 80% power and assuming a 5% significance level, a minimum total sample size per group of 64 is required. Assuming the GAD-Q-IV SD is 3.46 [49], the proposed sample size provides 80% power to detect a between-group effect corresponding to a GAD-Q-IV change of 1.73 points (or a Cohen’s *d* of 0.5 or greater). By targeting 100 students recruited per condition (N=300), even allowing for nearly 30% attrition, which is a possibility in Internet-based intervention trials, GAD-Q-IV mean differences between each active condition compared with the wait-list control condition will be detected with sufficient power. The difference in mean change between the two active conditions is not a primary comparison, as they are two different programs.

### The Interventions

#### Active Condition 1: “Lantern” Guided Self-Help Intervention

The Lantern Anxiety Program is a cognitive-behavioral intervention (CBT) that can be accessed via any Internet-enabled computer, mobile phone, or tablet via the Go Lantern website (Figure 2). The program includes psychoeducational content, interactive tools and exercises, symptom monitoring, and an online program coach who can monitor a user’s progress in the program and provide personalized feedback and encouragement via in-program messaging and voice calls. The program is based on an evidence-based, 14-session CBT for GAD intervention, developed by [name] [36,50,51]. CBT for GAD has been demonstrated to produce the largest effect sizes when compared to other therapy conditions such as analytic psychotherapy and nondirective therapy [52]. The CBT for GAD treatment includes (1) applied relaxation training, which involves the identification of early cues of anxiety, learning the skills of progressive relaxation (PR) and other relaxation techniques and learning how to apply relaxation to anxiety cues (called “applied relaxation,” [AR]); (2) imaginal rehearsal via self-control coping desensitization, using AR and alternative, nonanxious coping thoughts; and (3) cognitive therapy methods to help change how clients perceive, interpret, and believe, so that they will see less threat in the world and feel more confidence in their abilities to cope with the future.

Content is divided into 8 units, each with 5 sessions, resulting in 40 daily 10-minute sessions. The 8 units comprise an introduction to anxiety, automatic thoughts, cognitive reframing, introduction to behavior change, imaginal exposure, situational exposure, mindfulness, and habit formation. There are both cognitive (eg, worry tool, mindfulness) and behavioral (eg, progressive muscle relaxation, deep breathing, guided imagery) techniques taught in each module and always accessible thereafter. Users can access one session per day, with the next session unlocking only after the prior session is completed; therefore, less engaged users may not be exposed to all content. The program and program coach prompt users to schedule reminders to facilitate self-monitoring, encourage completion of scheduled activities, and promote use of tools and techniques in the program. Users can schedule reminders to complete sessions and to use techniques or self-monitoring entries at their desired frequency. They are prompted to do so after learning a new technique. Coaches can also schedule reminders for themselves to send users messages.

Students using Lantern will be guided through the program by mental health workers in India who have been trained to serve as online program coaches. To be eligible to be a coach, individuals must have some background and/or experience in psychology, have at least 6 months of supervised, in-person counseling experience, own a personal computer or smart device and check email daily, be comfortable with technology, and have a minimum of 3 hours per week to dedicate to coaching. A total of 20 potential program coaches were recruited, all of whom had completed a 6-month training course in the basic principles of psychological counseling from the Hyderabad Academy of Psychology based in Hyderabad, India.

A pretraining assessment was used to assess existing skill levels and inform training content development. To begin, 4 weeks of remote training covering basic foundational concepts was conducted. Manuals and papers reviewing CBT for GAD, panic disorder, and social anxiety were assigned, and a virtual discussion session was conducted each week via online collaboration platform GoToMeeting. In addition, coaches were provided a demo user account of the Lantern Anxiety Program so that they could familiarize themselves with the intervention content. Following remote training primarily reviewing content and basic concepts, a 3-day in-person training was conducted in Hyderabad, India, in December 2014. During this training, the Lantern coaching platform was introduced and coaches learned how to effectively interact with the coaching dashboard. The coaching dashboard enables coaches to monitor the activity and engagement of the students assigned to them as well as to send messages to them. Coaches were instructed on guided self-help coaching best practices, introductory phone call and messaging protocols, motivational interviewing, and risk management procedures.

Following training, coaches were assessed for comfort with technology via direct observation of their interaction with the Lantern coaching dashboard during interactive role plays. Coaches who demonstrated low technology fluency and experienced usability issues interacting with the coaching software in comparison with the group were asked to attend additional training and practice sessions to continue. Behavioral rehearsal tasks were used to evaluate coaches’ fidelity to the coaching protocol. Coaches were required to complete a mock introductory phone call with a control student (played by the research coordinator or volunteer students following a script), and fidelity to the phone call procedural checklist was assessed. Coaches were also required to respond to message prompts designed to assess their mastery of core competencies of CBT for GAD in the context of a guided self-help intervention. Their responses were rated against a messaging best practices checklist that was developed by the authors. Finally, coaches had to complete an established “e-therapist assessment” developed by the National eTherapy Centre (NeTC) at Swinburne University of Technology [53] and score at least 80%. Of the 20 trainees who began training, 65% (n=13) cleared the post-training evaluation and moved forward to become program coaches for this trial.

Throughout the intervention period, coaches will have on-going monitoring and support. Coaches must attend a weekly, live 1-hour supervision, during which coaches can present any challenging cases to the group and receive feedback from the coach clinical supervisor (a clinical instructor at Stanford and a licensed mental health care professional in the United States). Coaches will also be asked to submit 1 challenging message exchange per week to a clinical psychology doctoral student for individual feedback on messaging style and content. Finally, coaches can post questions and messages on a group listserv to get feedback from the supervisor as well as from peers.

#### Active Condition 2: “GAD Online” Pure Self-Help Intervention

The GAD Online program is also CBT based and can be accessed via any Internet-enabled computer, mobile phone, or tablet via the Mental Health Online website (Figure 3). Mental Health Online is a suite of online mental health programs developed and maintained by the NeTC at Swinburne University of Technology and funded by the Australian Federal Government Department of Health. The GAD Online program delivered in this trial, which was previously reported on as an Anxiety Online module [33], provides psychoeducation about GAD and techniques to reduce GAD symptoms (eg, relaxation, challenging thoughts, coping with worry, problem solving). The content covered in this program is comparable to that delivered in the Lantern GSH program. Content is divided into 12 modules, with 1 module per week being the suggested use; however, users can progress at their own pace. Unlike the design of the Lantern program, users can access other modules in the GAD Online program even if they do not complete the first module. Students are explicitly told they are not monitored and should contact the on-campus counselor should they require real-time support from a professional.

**Figure 2 figure2:**
[figure not shown]
Screenshot of Lantern Internet-based user view.

**Figure 3 figure3:**
[figure not shown]
Screenshot of Mental Health Online’s GAD Online program.

#### Wait-list Control Condition: Delayed Program

Students randomized to the wait-list control condition will complete surveys at the postintervention time point (3 months) and the follow-up time point (9 months). Following successful completion of these surveys, they will be allocated to one of the online interventions. Students will be assessed for whether they sought help from the on-campus counselor at each time point. The counselor’s contact information is available to all students across the campus.

### Minimization of Contamination

As randomization occurs within each college campus, there is a possibility of contamination, in that students could share their programs with each other. However, this type of contamination is not believed to be likely, as the programs are presented as personalized and private. Furthermore, because recruitment for this exploratory trial is occurring at 3 distinct colleges, selected more so due to partnership, comparability between sites is not known. Future, larger trials might consider randomization by college site.

### Measures

Outcome data will be collected at post-treatment (3 months) and 6-months follow-up (9 months). The 3-month outcome is the primary end point as the intervention delivery will be completed and the optimal effect of the treatment would be expected. The 6-month follow-up is included to evaluate the sustainability of the effect of the intervention. The outcome assessment measures are summarized in Table 1. Although the primary outcome measure is the GAD-Q-IV, we also assessed other anxiety disorders and potential functional impairments. Because only a few studies have gathered comprehensive data on prevalence rates of types of anxiety disorders and given the unique opportunity to administer an online survey to this large population, a subaim of this study and the involved stakeholders is to gather epidemiological data that can inform future research and policy and programmatic decisions by stakeholders to address the needs of students. Besides, given the high degree of comorbidity present among individuals who experience GAD [6,36,54], measuring psychological state and evaluating co-occurring disorders such as other anxiety disorders and depression are important. Finally, because CBT for GAD has been demonstrated to address symptoms associated with other disorders [47,55], both the prevalence and secondary outcomes are relevant. To ease anticipated survey burden, the survey is designed to use logic that allows for participants with low scores and fewer comorbid concerns to “skip” subsections. Demographic data will include gender, age, race/ethnicity, sexual orientation, religion, relationship status, family income, and hometown.

### Details of the Measurements

#### Generalized Anxiety Disorder Questionnaire (4th Edition)

The primary outcome is GAD symptom severity as measured by dimensional scoring of the 4th edition of the Generalized Anxiety Disorder Questionnaire (GAD-Q-IV) [42]. GAD caseness, as measured by categorical scoring of the GAD-Q-IV, is a secondary measure. The GAD-Q-IV is a 9-item self-report measure designed as an initial screen for the presence of GAD based on the DSM-IV. The GAD-Q-IV showed 89% specificity and 83% sensitivity when compared to structured interview diagnoses of individuals with GAD, social phobia, panic disorder, and a nonanxious comparison group. The GAD-Q-IV has demonstrated good test-retest reliability in a college sample over a 2-week assessment, with 92% of the sample showing stability across time with respect to GAD diagnosis [42].

#### Emotional Distress From Anxiety Measure

The Patient Reported Outcomes Measure Information System (PROMIS) Emotional Distress from Anxiety measure [56] is a reliable 8-item self-report measure to evaluate emotional distress from anxiety. This measure was included as a potential global outcome measure of improved quality of life.

#### Penn State Worry Questionnaire

The Penn State Worry Questionnaire (PSWQ) [57] is a 16-item self-report measure of the frequency and intensity of worry. The PSWQ has been shown to distinguish individuals with GAD from individuals with other anxiety disorders [58]. This measure was included to assess change in worry, a primary symptom of GAD.

#### Panic Disorder Self-Report

The Panic Disorder Self Report (PDSR) [44] is a 22-item self-report measure designed to diagnose panic disorder based on DSM-IV criteria. The PDSR showed 100% specificity and 89% sensitivity when compared with clinician-based ADIS-IV-L diagnoses of individuals diagnosed with panic disorder, GAD, social phobia, and a nonanxious comparison group. This measure, along with the other measures of anxiety disorders and depression, was included to assess both prevalence of this type of anxiety and the impact of the active interventions on symptoms associated with typically co-occurring disorders.

#### Social Phobia Diagnostic Questionnaire

The Social Phobia Diagnostic Questionnaire (SPDQ) [43] is a 10-item self-report measure designed to diagnose social phobia based on DSM-IV criteria. The SPDQ showed a specificity of 82% and a sensitivity of 85% when compared with clinician-based structured interview diagnoses of individuals meeting criteria for social phobia, panic disorder, and a nonanxious comparison group.

#### Post-Traumatic Stress Disorder Checklist

The Post-Traumatic Stress Disorder Checklist for DSM-V (PCL-5) [45] is a 20-item self-report measure that assesses the 20 DSM-V symptoms of PTSD. It was designed to monitor symptom change during and after treatment, screen individuals for PTSD, and make provisional PTSD diagnoses.

**Table 1 table1:** Scales to be administered at each time point.

Outcome variable			Measurement tool/data collection method	Time point (months)		
				0	3	9
Eligibility			Self-report	X		
Demographics			Self-report	X		
Field of study			Self-report	X		
Perceived social support			Self-report	X		
Belief in efficacy of online programs (credibility/expectancy)			Self-report	X		
Contamination			Self-report		X	
Grade point average			Self-report	X	X	X
**Primary outcome**						
	Difference in GAD symptom severity at postintervention and follow-up between the intervention groups and control group		4th edition of the Generalized Anxiety Disorder Questionnaire (GAD-Q-IV) (scored dimensionally)	X	X	X

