#### Outcome Analyses

A 3 condition × time mixed-design ANOVA will be conducted to examine both primary and secondary hypotheses. Using a mixed-design ANOVA will test for differences between 2 or more independent groups while subjecting participants to repeated measures. The model is a type of mixed effect model, with the fixed effects factor being a between-subjects variable and the random effects factor being a within-subjects variable. Follow-up paired comparisons will be conducted to specifically assess if there is significant differential change in GAD symptoms between each active condition and control from the baseline to the postcondition and follow-up assessments. Within- and between-group effect sizes will be calculated using Cohen’s *d* (based on the pooled standard deviation), specifically contrasting each active condition with the control condition for the main outcome.

Primary analyses will be undertaken using an intention-to-treat (ITT) approach, including all participants randomized regardless of treatment actually received, program engagement, or withdrawal from the trial. Using a mixed model design will allow us to include participants with missing data, which is likely to occur in large Internet-based trials.

Study site will be included as a covariate as this might have an influential effect given that the 3 sites were selected primarily based on accessibility versus between-site comparability. If some sites have poor recruitment, the data will be combined.

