Another limitation is that the primary outcome measurement tool, the GAD-Q-IV, and the associated diagnostic thresholds have been normed in US university student populations but not in an Indian university student population. One implication is that the prevalence of the disorder could be mischaracterized due to diagnostic criteria being interpreted differently cross-culturally. For example, the DSM-IV GAD criterion that anxiety be “excessive” might lead to underdiagnosis of GAD in developing countries in which worry is less likely to be reported excessive in the presence of comparatively more severe life concerns [70]. Using dimensional versus categorical scoring of the GAD-Q-IV to both determine eligibility and monitor for change in symptomatology, this concern might be partially addressed. The cutoff point of 5.7 was found to be overly sensitive in the US college population [42], so it is a reasonable threshold above which to initially allocate interventions to those potentially in need but not currently accessing services. However, future and parallel research should focus on validating the assessment tools.

Another potential limitation is the fact that the two active conditions differ both by the degree of coaching support and the program used, which precludes this study from clearly deducing the additional, if any, benefit of guidance. However, the primary hypothesis is that the use of one or both of the active interventions will lead to a greater GAD symptom reduction than the wait-list control. If the unguided program is found to be both feasible to disseminate to this population and relatively effective, future controlled studies can evaluate the comparative benefit of guidance and conduct cost-benefit analyses of delivering unguided versus guided programs. The conditions under which it is more or less effective will also be explored (eg, it might be more effective for those with higher reported motivation who are more likely to complete more of the program). The primary initial aim is an evaluation of the feasibility and efficacy of the model of survey-linked-to-online-interventions to reduce the incidence and prevalence of common mental health disorders in defined Indian university populations**.**

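### The primary endpoint is month 3 in some sections and months 3 and 9 in others, and the either-program claim has no stated error control across its two comparisons

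*Protocol article*

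**What the plan says.** On the time point, the protocol article gives two answers.

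- The Abstract names symptom severity at 3 months as the primary outcome. Measures agrees and gives a reason: "The 3-month outcome is the primary end point as the intervention delivery will be completed". It keeps the later assessment to judge whether the effect lasts.
- Table 1, under Primary outcome, has "Difference in GAD symptom severity at postintervention and follow-up between the intervention groups and control group". Sample Size Estimation is based on change from baseline to both later assessments. Outcome Analyses plans paired comparisons of change "between each active condition and control from the baseline to the postcondition and follow-up assessments".

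On what counts as success, the Abstract calls the difference of each program from the wait list a primary analysis. Objectives and Hypotheses speaks of either active program. Limitations restates the primary hypothesis as "the use of one or both of the active interventions will lead to a greater GAD symptom reduction than the wait-list control".

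On error and power, Sample Size Estimation says "the sample size is powered to detect at least a medium effect size of 0.5" and then "With 80% power and assuming a 5% significance level, a minimum total sample size per group of 64 is required". It recruits 100 per condition to allow for nearly 30% attrition. Outcome Analyses plans a condition-by-time mixed ANOVA with follow-up paired comparisons. It states no significance level, no adjustment, and no rule that the ANOVA must be significant first.

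**The concern.** The time-point conflict concerns the definition of the primary outcome. A reader who follows Measures would call a result seen only at month 9 secondary; a reader who follows Table 1 could call it primary. The Limitations wording adds a second route, because one successful program would satisfy the hypothesis. The primary claim may therefore rest on any of two tests (two programs at month 3) or any of four (two programs at two times), while the only significance level in the article is the 5% used to size one comparison. At stake is whether a month-9-only or single-program result could be reported as meeting the primary claim, and with what chance of error.

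**Working it through.** **Inputs from the article.** Effect size 0.5; "Assuming the GAD-Q-IV SD is 3.46"; "a between-group effect corresponding to a GAD-Q-IV change of 1.73 points"; 80% power; 5% level; 64 per group; 100 recruited per arm; 1:1:1 allocation; nearly 30% attrition.

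**Input assumed.** The correlation between the month-3 and month-9 contrasts is not given. It is varied from 0.3 to 0.9.

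**1. The plan's own figure.** 0.5 × 3.46 = 1.73 points, as stated. A two-sided 5% two-sample t test at d = 0.5 needs 63.8, so 64 per group, with power 80.1%. A one-sided test would need about 50 (normal approximation), so the 5% is two-sided. Attrition: 64 / 0.70 = 91.4, so 92, below the 100 planned. The figure is correct for one comparison.

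**2. Two programs at month 3.** Equal arms sharing one control give contrasts Z1 and Z2 with correlation 0.5. Under no effect, 1 − P(|Z1| < 1.96 and |Z2| < 1.96) = 9.1%. Independence would give 1 − 0.95² = 9.75%. Counting only results that favour a program, 1 − P(Z1 < 1.96 and Z2 < 1.96) = 4.5%.

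**3. Two programs at two times.** The same calculation for four contrasts, by multivariate-normal simulation with 1,000,000 draws:

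| Between-time correlation | Any of four, two-sided | Any of four, benefit only |
|---|---|---|
| 0.3 | 16.9% | 8.5% |
| 0.5 | 16.1% | 8.1% |
| 0.7 | 14.8% | 7.4% |
| 0.9 | 12.6% | 6.3% |

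**4. If the ANOVA were a binding gate.** Under no effect anywhere, the chance of passing the gate and then finding a significant contrast is about 4.1% with month 3 alone. With both times it is 4.3% to 3.8% (correlation 0.3 to 0.7). If one program works at month 3, the chance of a false positive for the other under the two-time gate is 9.4% to 8.1%. That last case takes the working program's contrasts at both times as 2.83 standard errors, which is 0.5 / √(2/64).

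**5. Power if the two month-3 contrasts are adjusted.** Dunnett's two-sided critical value at correlation 0.5 is 2.212, a per-test level of 0.027. At d = 0.5:

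| Evaluable per arm | Unadjusted 5% | Dunnett |
|---|---|---|
| 64 | 80.1% | 72% |
| 70 (30% attrition) | 84% | 76% |
| 76 (24% attrition) | not needed | 80% |

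Dunnett needs 75.8, so 76 per arm, and 1 − 76/100 = 24% attrition. If the claim is for at least one program and both have d = 0.5, the chance that at least one wins at 64 per arm is about 92% unadjusted and about 87% with Dunnett.

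**The case against.** Several points on the other side have force.

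- **Unadjusted testing is an inference.** The only 5% is the sizing input. A statistical analysis plan, not shown here, could add an adjustment. This stands, so the error rates are conditional on testing each contrast at 5%. Such a plan would still inherit two definitions of the primary time point, and any adjustment would change the power and attrition statement.
- **The ANOVA may be meant as a gate.** Calling the paired comparisons follow-up tests suggests it. A gate would hold the error near 5% when nothing works, and with three arms at one time it controls the familywise rate. But the article does not make it a condition, and with two times it does not protect the second program once the first works.
- **The claim is directional.** A program worse than the wait list cannot satisfy it, so the rate of falsely claiming benefit is about half the two-sided figure. This stands.
- **Month 3 is the better-supported reading.** Measures gives a reason for it, and Table 1's caption presents a schedule of scales. This favours month 3 as the answer, but the other two sections also use both times.
- **Two distinct programs may not need joint control.** The article calls the trial exploratory and the arms two different programs, and whether such comparisons need correction is debated. With a separate claim for each program the case for adjustment is weak. The one-or-both wording is where it becomes strong.

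A reader might infer that the trial has a 9-17% chance of a false win, or that it is underpowered. The documents support neither. The first counts results in the wrong direction and assumes unadjusted, ungated testing. The second overlooks that 80% at 64 per arm is correct for the comparison described, and that nearly 30% attrition is tolerable under that test. The article also expects effects of 0.62 to 1.07, above the 0.5 used for sizing.

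**Conclusion.** The article contradicts itself on the primary time point, and it leaves open whether success means each program or at least one. Both affect what the trial may conclude, and both lie in the protocol's own wording rather than in detail left to a later plan.

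The size is conditional. With each contrast tested at 5%, the two-sided familywise error is about 9% for month 3 alone and about 13-17% with month 9 included; false claims of benefit alone are about 4.5% and 6-8.5%. The month-3 figures follow from equal allocation and a shared control. The four-test figures also rest on the assumed between-time correlation. The sample-size calculation contains no arithmetic error; its power and attrition statement changes only if an adjustment is adopted.

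**What to change.** 1. Make GAD-Q-IV severity at month 3 the sole primary time point in Table 1, Sample Size Estimation and Outcome Analyses, as in the Abstract and Measures. List month 9 as secondary.
2. State in Objectives and Hypotheses and in Limitations whether the primary claim is made for each program separately or for at least one.
3. If at least one suffices, test the two active-versus-wait-list contrasts at month 3 with Dunnett or Holm at familywise 5%, and say that they do not depend on the ANOVA result.
4. Keep N=300. If Dunnett is used, restate the power as 80% per comparison at 76 evaluable per arm (24% attrition), or about 76% at 30% attrition.

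The cost is wording, plus a slightly less favourable stated power or attrition tolerance. Recruitment and assessments do not change.
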